##### 2.4.2.2.Postoperative intensive PR

Postoperative PR starts one month after surgery and includes 39 sessions divided into 15 outpatient sessions performed twice a week and 24 home-based sessions performed three times per week. Overall, the postoperative PR programme lasts 8 weeks.Each outpatient session takes approximately two hours and 15 min and includes both aerobic and resistance training, following the same procedures described for preoperative PR, plus RMT for the first eight sessions. In addition, outpatient postoperative PR includes 10 min of scar massage during the first four weeks and group bodyweight exercise training, scheduled once a week for the entire duration of the programme.Each home-based session lasts approximately one hour and consists of an individual, unsupervised and personalised combination of RMT performed twice a day and 30 min of aerobic walking at the intensity of 60–80% of maximal heart rate, monitored by patients with the portable device provided. Once again, patients are requested to record their adherence to home-based training by the training log.

At the end of postoperative PR, patients are advised to continue aerobic training and RMT until the 6-month follow-up is completed (T3).

### Standardization of procedures

All other aspects of patient management, such as perioperative care, general anaesthetic, intraoperative airway management and ventilation settings, postoperative analgesia, perioperative care and discharge plans, are routinely performed according to the current institutional protocols.

In particular, analgesia is provided and reviewed by the anaesthesiologist team and involves the positioning of epidural catheter before induction. Naropine 500 mg + Morphine 20 mg are administered though epidural catheter for the first 48 h, starting at the end of surgical procedure, with paracetamol 1 g every eight hours and ketoprofen 1 fl intravenously. Epidural catheter is removed usually on the third day after drainage elimination and therapy is shifted per os until discharge. Pain killer reduction is started one week after discharge.

To ensure the highest level of standardization of both the administration of treatments and the evaluations, two physiotherapists have been specifically trained for the purpose of this study; they are also responsible for collecting data regarding the outcome measurements (i.e., 6MWT, SF-12, HADS, NRS).

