##### 1.2.1.1.Primary outcome measure

The primary outcome measure to assess the superiority of intensive PR over standard care (SC) is the change in distance walked in six minutes (6MWD) measured six months after surgery, compared to baseline.

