#### Control group

Patients allocated to CG receive SC, which consists of one therapeutic education session delivered by physician and physiotherapist the day before surgery and early inpatient postoperative PR, delivered by physiotherapist. The therapeutic educational session lasts 30 to 40 min and involves counselling and self-care management. The aim of counselling is to prepare the patients for the postoperative course, emphasising breathing exercise and sputum clearance techniques, pain control strategies and self-care. More specifically, breathing exercises focus on diaphragmatic breathing to prevent or relieve discomfort (shortness of breath, anxiety, pain), deep breathing to better ventilate all lung lobes and clearance techniques (huffing). These techniques are explained and repeatedly performed until the patient has mastered them. Self-care management involves pain relief and postural advice, as well as mobility techniques and practical advice in order to better cope with post discharge issues which could arise at home.

From day 1 after surgery until discharge patients receive daily early inpatient postoperative PR, which includes breathing exercises and positive expiratory pressure training with PEP bottle (PEP training) for a duration of 30 to 40 min every day. Upon discharge, patients are advised to continue breathing exercises and maintain an active lifestyle.

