#### Intervention group

Patients allocated to the IG receive SC plus intensive PR, which includes a total of 53 sessions (14 preoperative and 39 postoperative).

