#### Randomization procedure

Patient enrolment is performed by the study data managers or physicians with a phone call to the local Research and Statistics Unit, which generated the allocation sequence: the responder simultaneously enters the patient and caller names and uses a predefined randomization list to make the assignment. Group allocation is revealed to researchers performing interventions and to patients after baseline evaluations (T0) are completed.

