#### Blinding

This is an open-label study, due to the limited number of professionals involved in a single institution project.

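### The two physiotherapists trained to give the study treatments also collect the primary 6MWT and the SF-12, HADS and NRS after allocation is known, and no masked or non-treating assessor is planned

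*Protocol article*

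**What the plan says.** Standardization of procedures links treatment and measurement in one sentence: "To ensure the highest level of standardization of both the administration of treatments and the evaluations, two physiotherapists have been specifically trained" for the study, and "they are also responsible for collecting data regarding the outcome measurements (i.e., 6MWT, SF-12, HADS, NRS". The 6MWT supplies the primary endpoint, which "is the change in distance walked in six minutes (6MWD) measured six months after surgery, compared to baseline".

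The Randomization procedure section states when the arm becomes known: "Group allocation is revealed to researchers performing interventions and to patients after baseline evaluations (T0) are completed". The Blinding section consists of one sentence: "This is an open-label study, due to the limited number of professionals involved in a single institution project". It mentions no masked assessor and no separation of treating and assessing staff.

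Contact with physiotherapists differs between arms. For the intervention group: "Patients allocated to the IG receive SC plus intensive PR, which includes a total of 53 sessions (14 preoperative and 39 postoperative". Of these sessions, 6 preoperative and 15 postoperative ones are outpatient. The control group receives standard care, "which consists of one therapeutic education session delivered by physician and physiotherapist the day before surgery and early inpatient postoperative PR, delivered by physiotherapist".

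**The concern.** The patients cannot be blinded here, and that is no fault of the plan. Who holds the stopwatch is a separate matter. The plan gives outcome collection to the people trained to administer the treatments, at visits where they know the arm. Distance walked in six minutes depends partly on effort and on how the test is led. This is general knowledge about the test and not a statement in the protocol. If the assessor encourages one arm a little more, or if familiarity makes those patients try harder, the difference enters the endpoint as if it were a treatment effect. The likely direction is towards the intervention, which is also the direction of the superiority claim, though that direction is not certain.

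The same two people collect SF-12, HADS and NRS, where the way a form is administered can influence the answers.

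The reason given in the Blinding section, a small number of professionals, may explain why staff cannot all be masked. It does not require that a patient's own therapist assess that patient, because the protocol names two trained physiotherapists.

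**Working it through.** **Which measurements are exposed.** Setting the Measurements section and its Table 2 beside Standardization of procedures and Randomization procedure gives:

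| Outcome | Collected by the two physiotherapists? | Time points after allocation is known |
|---|---|---|
| 6MWT (primary at six months) | Yes | One and six months |
| SF-12 | Yes | Six months |
| HADS | Yes | Day before surgery, six months |
| NRS | Yes | One and six months |
| FEV1, FVC, DLCO | Not in their list; assessor not named | – |
| Length of stay, complications, 30-day mortality | Not in their list; recorder not named | – |

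All baseline values are taken before randomization.

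**Why the change score does not help.** Let b be the mean between-arm difference in six-month 6MWD that is due only to how the test is led. Baseline is measured before the arm is known and carries no such term. The expected difference in change (six months minus baseline) is therefore the true effect plus b. The independent-samples t-test estimates this sum and cannot split it.

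**Contact in the intervention arm beyond standard care.** 6 outpatient sessions by the one-month visit, and 6 + 15 = 21 by six months.

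**The plan's own sample size.** From the Sample size section: difference 25 m, d = 0.5, 5% type I error, 80% power, 10% dropout.

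- Implied SD = 25 / 0.5 = 50 m.
- n per arm = 2 × (1.960 + 0.842)² × (50 / 25)² = 62.8, so 63 per arm and 126 in total. The t-based solution is 63.8, so 64.
- With dropout: 126 / 0.90 = 140. The stated 140 reproduces.

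**Illustration of sensitivity.** Assumptions: no true effect, SD 50 m, 63 per arm, two-sided 5% test (the article states two-sided confidence intervals but not the sidedness of the test). The shifts b are assumed, because the documents give none.

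- SE of the difference = 50 × √(2/63) = 8.91 m.
- Smallest significant difference ≈ 1.96 × 8.91 = 17.5 m.
- Chance of a significant result favouring the intervention = 1 − Φ(1.96 − b / 8.91).

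| Assumed shift b | b / 8.91 | Normal approximation | t-test |
|---|---|---|---|
| 0 m | 0 | 2.5% | 2.5% |
| 5 m | 0.56 | 8.1% | 8.0% |
| 10 m | 1.12 | 20.1% | 19.9% |
| 15 m | 1.68 | 39.1% | 38.6% |

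Counting significance in either direction, the normal approximation gives 8.7%, 20.2% and 39.1% against a nominal 5%. Relative to the 25 m target, the three shifts are 20%, 40% and 60% of the effect that the trial is designed to detect.

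**The case against.** Several points on the other side have force.

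- **A reader might infer that these two measure every outcome.** The article does not say so. Their list is 6MWT, SF-12, HADS and NRS. Lung function, length of stay, complications and mortality are outside it.
- **A reader might infer that all measurements are made with the arm known.** Baseline is not, because allocation is revealed only afterwards.
- **A reader might infer that the same two people deliver all 21 outpatient sessions and treat only the intervention arm.** The text says they were trained to standardize the administration of treatments. Delivery of the intensive sessions is the natural reading, but it is not stated. Controls also receive physiotherapy, possibly from the same people. The difference in contact is documented; who provides it is not.
- **The 6MWT follows current guidelines, according to Measurements.** These may already fix how patients are encouraged, and the article does not show whether they do. Standardizing the test would still not mask the person leading it.
- **The patient-reported outcomes come from patients who know their arm.** Changing the collector removes only the effect of administration. Whether the forms are self-completed is a detail that an article may leave to the full protocol, and it is not criticised here.
- **Masking between two colleagues will often fail.** Intervention patients attend outpatient sessions and weekly group training, while controls have no outpatient programme. Shuttle and 10-repetition maximum tests at one month, and the recording of adherence and side effects at other visits, also reveal the arm. An assessor outside the programme would be masked more reliably, but would need the staff that the Blinding section says are limited.

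These points narrow the concern and limit what a remedy can achieve. They leave intact that the post-randomization 6MWT is assigned to staff trained to treat, with no provision for a non-treating assessor.

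**Conclusion.** The concern holds for the 6MWT, including the primary endpoint, and in part for SF-12, HADS and NRS, at assessments after allocation is revealed. It is a weakness that the plan fixes in its text, because it assigns evaluation to the people trained for treatment. The stated shortage of professionals does not justify a therapist assessing his or her own patients.

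The size of any bias is unknown. The figures of about 8%, 20% and 39% show how sensitive the test is to shifts of 5, 10 and 15 m under the assumptions listed. They are not evidence that such shifts occur. They do show that a shift well below the 25 m target would matter and that the planned analysis could not detect or correct it. The sample size is unaffected. The change is worth making because it is cheap and bears on the primary endpoint.

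**What to change.** Amend Standardization of procedures, for every patient still to be assessed, as follows:

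1. Each patient has one of the two physiotherapists designated as treating. The other runs that patient's one-month and six-month 6MWT, is not told the arm where this is feasible, and uses the same scripted encouragement in both arms.
2. The treating physiotherapist does the arm-specific tasks (shuttle test, 10-repetition maximum test, recording of adherence and side effects) separately from the 6MWT.
3. SF-12, HADS and NRS are completed by the patient without the treating physiotherapist present.

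The Blinding section should then say that treatment is open-label and describe who assesses the 6MWT.

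The cost is rostering and about one paragraph of text, with no added staff, visits or patients. The downsides are some scheduling constraint, masking that will often be incomplete, and only partial gain for the patient-reported outcomes. Enrolment began in 2015, so patients already assessed keep the old procedure, and the date of the change should be recorded.

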### Withdrawal from trial

Participation in the study will be withdrawn if any of the following occurs:Patient referred for adjuvant treatmentPatient lost to follow-upPatient withdrawal of consentDeath of the patient

All withdrawals are recorded specifying the reason.

### Statistical considerations

#### Sample size

Since data for mean and standard deviations of 6MWT after lung surgery with or without treatment have never been published, Cohen’s medium effect size (d = 0.5) has been used to compute sample size based on the minimal significant variation reported (25 m) [33].

We also expect a potential dropout rate of about 10% for the aforementioned reasons. Thus, assuming 5% type I error and 80% power for this study, we plan to enrol 140 patients (about 70 patients in each arm).

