**Methods:**

We describe the study protocol for the open-label randomized controlled trial we are conducting on patients affected by primary lung cancer (stages I-II) eligible for surgical treatment. The control group receives standard care consisting in one educational session before surgery and early inpatient postoperative physiotherapy. The treatment group receives, in addition to standard care, intensive rehabilitation involving 14 preoperative sessions (6 outpatient and 8 home-based) and 39 postoperative sessions (15 outpatient and 24 home-based) with aerobic, resistance and respiratory training, as well as scar massage and group bodyweight exercise training.

Assessments are performed at baseline, the day before surgery and one month and six months after surgery. The main outcome is the long-term exercise capacity measured with the Six-Minute Walk Test; short-term exercise capacity, lung function, postoperative morbidity, length of hospital stay, quality of life (Short Form 12), mood disturbances (Hospital Anxiety and Depression Scale) and pain (Numeric Rating Scale) are also recorded and analysed. Patient compliance and treatment-related side effects are also collected. Statistical analyses will be performed according to the intention-to-treat approach. T-test for independent samples will be used for continuous variables after assessment of normality of distribution. Chi-square test will be used for categorical variables. Expecting a 10% dropout rate, assuming α of 5% and power of 80%, we planned to enrol 140 patients to demonstrate a statistically significant difference of 25 m at Six-Minute Walk Test.

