## Methods

### Study design

A single institution 1:1 randomized controlled open-label trial with two parallel arms, powered for superiority, has been designed in accordance with the CONSORT statement and Helsinki declaration. The study has been approved by the local Ethical committee [n. 2013/0009390] and funded by the Italian Ministry of Health [GR-2011-02351711].

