#### Statistical analysis

Statistical analyses will be performed according to the intention-to-treat approach. Statistical techniques per study aims are as follows:
*Primary aim:* t-test for independent samples to compare the mean of the change (defined as T3 – T0 related date) in 6MWD between IG and CG. In case of heteroscedasticity, checked by folded F test, the Satterthwaite adjustment will be used.
*Secondary aims*:- t-test for independent samples to compare the mean of the change between IG and CG for 6MWD (T2 – T0 change), FEV1, FVC, DLCO and SF-12 score (T3 – T0 change), HADS score (T1 - T0 and T3 - T0), NRS score (T2 – T0 and T3 – T0) and LoS. In case of heteroscedasticity, checked by folded F test, the Satterthwaite adjustment will be used.- chi-square test to compare the proportion of postoperative complications between IG and CG;

Five percent significance will be used to assess the *p*-values and 95% two-sided confidence interval will be provided for each tested parameter; the confidence intervals will be calculated assuming normal distribution.

Statistical calculations will be performed by the local Research and Statistics Unit using SAS System release 9.2 or later, R release 3.3.3 or later, SPSS release 23 or later, according to the availability at the time of the data analysis.

Patient adherence to protocol may be a crucial issue in determining the efficacy of rehabilitation programmes, including exercise training. Although it has not been plainly demonstrated, in principle, non-attendance could affect exercise dose and influence the outcome of treatment [34]. Therefore, if patient compliance, is less than 80% [25], we will proceed with a second per-protocol analysis.

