The definition of the best PR treatment programme required a careful review of the current literature [23], resulting in the definition of the following key elements:The inclusion of both aerobic and strength training of lower and upper limb muscles [2, 11, 35];The combination of outpatient and home-based treatment sessions. This should facilitate the enrolment of patients referred from provincial hospitals and might increase their compliance, minimizing the risk of attrition bias;The inclusion of inspiratory muscle training, incentive spirometry, airway clearance techniques and/or respiratory exercises, as lung cancer leads to respiratory impairment and COPD is a frequent comorbidity in patients affected by lung cancer [19, 20, 36, 37];The inclusion of group exercise training sessions during the postoperative phase, alongside individual guided and monitored home-based training, to facilitate mutual support among patients with NSCLC, whose vulnerable psychosocial condition could affect postoperative functioning and QoL [38]. In fact, a recent systematic review examining the spectrum of health care needs among people with lung cancer showed that psychological, emotional and social needs were most frequently specified and lack of acknowledgement of patients’ status by others were perceived as important issues [39]. Therefore, group sessions may facilitate the sharing of feelings, experiences and concerns, and may support patients in coping with their illness;The inclusion of scar massage in the postoperative phase to relieve tissue tension and reduce pain. In our clinical experience, patients frequently report pain and hypersensitivity around surgical scar.

At the time of planning this protocol, we estimated an overall 10% withdrawal rate, mainly due to perioperative morbidity and mortality, as well as unforeseen N1/N2 lymph nodal involvement diagnosed after surgery and requiring adjuvant therapies. However, more recent literature suggests a greater incidence of intraoperative lymph nodal upstaging [40] and even when an accurate staging workup is performed, including PET/CT and EBUS-TBNA when appropriate, minimal involvement of hilar nodes (N1 stage) remains difficult to assess preoperatively. Furthermore, more aggressive protocols are recommended by international guidelines in treating N1 NSCLC [41]. A greater than expected number of patients may therefore withdraw post randomization to ensure they receive the best cancer care.

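### The 140 patients follow from the stated inputs, but 80% power for a 25 m difference rests on an unstated SD of 50 m and on a 10% dropout rate that the protocol says may be exceeded

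*Protocol article*

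**What the plan says.** The design is described under Study design as "A single institution 1:1 randomized controlled open-label trial with two parallel arms, powered for superiority". The Sample size section explains that "data for mean and standard deviations of 6MWT after lung surgery with or without treatment have never been published", and that Cohen's "medium effect size (d = 0.5) has been used to compute sample size based on the minimal significant variation reported (25 m" metres being the reported minimal variation. It adds a dropout allowance of about 10% and concludes: "Thus, assuming 5% type I error and 80% power for this study, we plan to enrol 140 patients (about 70 patients in each arm". The Abstract (Methods) puts the same design in metres: "we planned to enrol 140 patients to demonstrate a statistically significant difference of 25 m at Six-Minute Walk Test".

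Three other places bear on these figures:

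- **Statistical analysis.** The primary test is a two-sample t-test on the T3 minus T0 change in walking distance, so the SD that matters is that of the change.
- **Withdrawal from trial.** Referral for adjuvant therapy counts as a withdrawal.
- **Discussion.** The 10% was the estimate when the trial was planned. The text then cites later evidence of more nodal upstaging and stronger guideline recommendations for treating N1 disease, and concludes: "A greater than expected number of patients may therefore withdraw post randomization to ensure they receive the best cancer care".

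No SD for walking distance, or for its change, is given anywhere. Neither the power nor the 140 is revised in light of the Discussion.

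**The concern.** A standardised effect and a difference in metres are interchangeable only through an SD. The protocol says that it has no such SD, takes d = 0.5 by convention, and still makes the claim in metres. The design is therefore powered for half an SD of the change, whatever that turns out to be in metres.

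The dropout allowance raises a second question. The 140 leaves no margin above 10%, yet the Discussion gives specific reasons why withdrawals may run higher, and the statistical section does not take them up.

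The stated power is a figure that readers will use when they interpret the result. If the trial is not significant, a reader may conclude that a 25 m benefit was sought with 80% power and not found. The document does not give enough to support that reading.

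**Working it through.** **Inputs.** Alpha and power come from the Sample size section ("assuming 5% type I error and 80% power for this study"). That section does not say one- or two-sided. Two-sided is taken from the Statistical analysis section ("95% two-sided confidence interval will be provided for each tested parameter"), and a one-sided calculation gives 50 per arm, which does not match the plan. Effect size d = 0.5, difference 25 m, 1:1 allocation and 10% dropout are as stated.

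**Step 1: reproduce the plan's figure.** By the normal approximation:

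n per arm = 2(z₀.₉₇₅ + z₀.₈₀)²/d² = 2(1.960 + 0.842)²/0.25 = 62.8, rounded up to 63.

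Total 126, and 126/(1 − 0.10) = 140. This is an exact match. The exact t calculation needs 63.8, so 64 per arm, 128 in total, and 128/0.9 = 142.2, so 143. The difference between the two formulas is trivial.

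**Step 2: the SD implied by 25 m.** SD = 25/0.5 = 50 m. Entering 25 m and 50 m directly also gives 63 per arm. No other SD makes the two targets agree.

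**Step 3: margin for attrition.** With 70 randomised per arm, 63 remain at 10% loss. Power there is 80.1% (normal) or 79.5% (exact t). The largest loss that keeps 80% is 1 − 63/70 = 10.0% (normal) or 1 − 64/70 = 8.6% (exact t). There is no slack.

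**Step 4: power for d = 0.5 by attrition.** Rates above 10% are assumptions; the protocol gives no alternative rate.

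| Attrition | Evaluable per arm | Power, normal | Power, exact t |
|---|---|---|---|
| 10% | 63 | 80.1% | 79.5% |
| 15% | 59.5 | 77.9% | 77.2% |
| 20% | 56 | 75.4% | 74.6% |
| 25% | 52.5 | 72.6% | 71.8% |
| 30% | 49 | 69.7% | 68.8% |

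If the SD were 50 m, the difference detectable with 80% power (exact t) would be 26.7 m at 20% attrition and 28.6 m at 30%.

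**Step 5: power for 25 m by SD of the change (exact t).** All SDs are assumptions and are shown on both sides of 50 m.

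| SD of change | d for 25 m | 10% attrition (63 per arm) | 20% (56) | 30% (49) |
|---|---|---|---|---|
| 40 m | 0.625 | 94% | 91% | 86% |
| 50 m | 0.500 | 79.5% | 74.6% | 68.8% |
| 60 m | 0.417 | 64% | 59% | 53% |
| 70 m | 0.357 | 51% | 47% | 42% |

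The claim in metres is far more sensitive to the SD than to attrition. Moving the SD from 50 to 60 m costs about 15 points at 10% attrition; moving attrition from 10% to 20% costs about 5 points at d = 0.5.

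**The case against.** Much can be said for the plan. Its sample size is computed correctly and delivers the stated 80% under its own inputs; 79.5% against 80.1% is only a choice of formula. The lack of SD data is disclosed, and anyone can divide 25 by 0.5. The withdrawal risk is discussed openly. The planned 95% confidence interval, rather than the planning power, will show whether 25 m is excluded. Enrolment began in 2015, so the Sample size section partly records how the 140 was chosen.

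All of this is true, and it rules out three stronger readings that a reader might infer:

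- **That 80% power is not delivered, or that the sum is wrong.** It is not wrong. A shortfall appears only with attrition above 10% or an SD above 50 m.
- **That the protocol admits that 10% is too low.** The Discussion says that more patients than expected may withdraw. It gives no rate and does not retract the 10%.
- **That the SD exceeds 50 m, so that power for 25 m is poor.** Nothing in the document places the SD above or below 50 m. At 40 m, power for 25 m would be about 94%.

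Disclosure does not settle the matter, however. The Abstract makes the claim in metres without the condition it depends on, and the Discussion's doubt about the 10% is never carried back to the power statement. The confidence interval will guard a careful reader against misreading a null result, but it does not make the stated power supported.

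**Conclusion.** The concern holds as a mismatch between a claim and its assumptions; it is not an arithmetic error. The 140 gives 80% power for a difference of 0.5 SD at 10% attrition. The claim of 80% power for 25 m is unsupported because it needs two conditions: an SD of the T3 minus T0 change of 50 m, which is neither stated nor justified, and dropout of no more than 10%, which the protocol itself says may be exceeded.

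If attrition were 20% to 30%, power for d = 0.5 would be 74.6% to 68.8%, a modest loss. For 25 m with 63 per arm, assumed SDs from 40 to 70 m give powers from about 94% down to 51%. That range describes what is unknown. It does not show a deficit, since the true SD could lie on either side of 50 m.

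**What to change.** 1. **Restate the power in the Abstract and the Sample size section.** For example: *140 randomised patients give about 80% power for a difference of 0.5 SD at 10% attrition, 75% at 20% and 69% at 30%; this corresponds to 25 m only if the SD of the T3 minus T0 change is 50 m.* Alternatively, drop the claim in metres. A small table by SD, covering values below and above 50 m, would help.
2. **Reconcile the 10% allowance with the Discussion.** Either justify keeping it or give the range of attrition now expected and the power that goes with it.
3. **Compute the SD of the change from accrued data, pooled over arms, and report the detectable difference it implies.** Ignoring arm reveals no treatment effect and inflates the SD only slightly: with a true SD of 50 m and a true difference of 25 m, the pooled value is √(50² + 25²/4) = 51.5 m.
4. **Make the primary analysis T3 walking distance adjusted for baseline walking distance, fixed before any comparison by arm.** Baseline distance is already collected at T0. With equal SDs at both visits and correlation ρ between them, the variance relative to the change-score analysis is about (1 + ρ)/2. This cannot lose precision to any material extent, but the gain is small if ρ is high. The documents do not give ρ, so no particular recovery of power can be promised.

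More patients are not requested. Holding 80% for d = 0.5 would take 158 (exact t: 160) at 20% attrition and 180 (exact t: 183) at 30%, but the document gives neither a revised rate nor an SD on which to base a new number. Whether patients referred for adjuvant therapy should still be assessed at six months is a separate question about the withdrawal rule and is not part of this fix.

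The cost is some rewording, one pooled SD calculation and a change to the primary model. The downside is a less favourable stated power.
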